#### Secondary outcomes

The secondary outcomes are all-cause mortality, functional status, health status, health-related quality of life (hrQoL), healthcare utilisation within 1 year of follow-up and costs of care (table 1).

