##### Preparation of the statistical model

As a first step, we describe how the overall effect of offering any type of telemedicine versus not offering telemedicine will be estimated. This analysis will subsequently be used for a comparison of telemedicine effects on days alive without unplanned HF-related hospitalisation during 1 year across subgroups.

The cohort is restricted to individuals with newly diagnosed HF, that is, at most 3 months prior to baseline. The exposure contrast is defined as offering any type of telemedicine after first presentation with HF at the hospital outpatient clinic versus patients not offered telemedicine. The telemedicine status for the entire follow-up is defined by 6 months after baseline measurement of telemedicine, used as an observational analogue of an ‘intention to treat’ analysis in which the stopping of telemedicine is disregarded.

Because telemedicine administration is dependent on patient characteristics, confounding by indication will be accounted for. Based on clinical consensus, the following patient-level confounding variables measured at baseline will be adjusted for: age, sex, SES, BMI, NYHA, LVEF, aetiology of HF, systolic blood pressure, diastolic blood pressure, heart rhythm, heart rate, chronic respiratory disorders, OSAS, stroke, extra cardiac arterial vascular pathology, DM, hypertension, anaemia, CKD, malignancy, heart rhythm disorders, depression and thyroid disease (see table 3 and online supplemental material 1).

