The primary outcome model is a linear mixed model with a random intercept for the participating centre and is specified as follows. The outcome is measured in days, and because the final measurement may be less or more than 365 days after baseline, we rescale the number of days of unplanned hospitalisation to the number of days under follow-up to 365 days. The outcome is computed by subtracting the days of unplanned hospitalisation or death from 365. The earlier described confounding variables are added to the primary outcome model to adjust for confounding. Continuous covariates are modelled using splines. Multicollinearity between confounding variables and the telemedicine status is evaluated. The coefficient for telemedicine in the primary outcome model represents the average treatment effect of offering any telemedicine within 3 months after HF diagnosis compared with not offering telemedicine on days with unplanned HF-related hospitalisation during a year in the population of patients with newly diagnosed HF. Robust SEs are estimated to compute CIs.

For the secondary outcome functional status, a similar approach is taken to estimate the average treatment effect of offering any telemedicine within 3 months after HF diagnosis compared with not offering telemedicine on functional status after 1 year in the population of patients with newly diagnosed HF. For this analysis, the outcome model is a multinomial regression model, and baseline functional status is added as a covariate. The risk difference relative to the reference outcome category is assessed using the predicted outcomes of the primary outcome model offering of telemedicine versus not offering, to obtain the marginal risk difference.^38–40^ Similarly, for the secondary outcomes health status and hrQoL, the outcome model is a probit regression model, with baseline measurements added as a covariate. Healthcare utilisation will be assessed using a Poisson regression model, and all-cause mortality will be assessed using binary logistic regression.

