##### Research question 1: effectiveness of telemedicine in patient subgroups

Research question 1 investigates the effectiveness of telemedicine across subgroups of patients with HF. Patient-related subgroups were identified by a systematic literature review of randomised controlled trials (RCTs) of telemedicine: age, severity of HF (NYHA class at baseline), sex, SES, presence of depression, atrial fibrillation and type of HF (HF with preserved ejection fraction (HFpEF), HF with midrange ejection fraction (HFmrEF), HF with reduced ejection fraction (HFrEF)) (table 3).^20–24 41–49^ Stratified analyses of the primary outcome model are performed to estimate the above-defined average treatment effect in each of the subgroups. Heterogeneity in telemedicine effect across age is assessed on a continuous scale, where an interaction between age and telemedicine status is added to the primary outcome model, and the expected number of days out of hospital across age ranges from 50 to 90 years is predicted from this model under telemedicine offered versus not offered.

In an additional analysis, heterogeneity across time since diagnosis is explored for the entire cohort, without restricting to patients with a maximum of 3 months since HF diagnosis at baseline (diagnosed ≤3 months before baseline compared with >3 months before baseline).

The secondary outcomes functional status, health status and hrQoL are assessed using similar approaches but using multinomial, probit and probit regression model, respectively. Healthcare utilisation will be assessed using a Poisson regression model, and all-cause mortality will be assessed using binary logistic regression.

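### If the full confounder set is refitted by unpenalised logistic regression for mortality within small subgroups, a real effect would be exaggerated there and could look like heterogeneity

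*Protocol article*

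**What the plan says.** All places are in the protocol article.

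- *Secondary outcomes* makes all-cause mortality within 1 year a secondary outcome.
- *Research question 1* states that "all-cause mortality will be assessed using binary logistic regression". *Preparation of the statistical model* and *Research question 2* name the same model.
- *Preparation of the statistical model*, before naming any outcome model, says that "the following patient-level confounding variables measured at baseline will be adjusted for" and lists 23 variables from age to thyroid disease. It then says of the primary linear mixed model: "The earlier described confounding variables are added to the primary outcome model to adjust for confounding". In the same paragraph: "Continuous covariates are modelled using splines".
- *Research question 1* sets the subgroup method: "Stratified analyses of the primary outcome model are performed to estimate the above-defined average treatment effect in each of the subgroups". The subgroups are NYHA class, sex, SES, depression, atrial fibrillation and HF type. Age is handled by a continuous interaction instead.
- For functional status, predictions with and without telemedicine are used "to obtain the marginal risk difference". No such step is named for mortality.
- *Research question 2* adds six hospital-level confounders and restricts the analysis to patients who received telemedicine.
- The abstract calls the stratified analyses exploratory.

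**The concern.** A linear model with about 40 covariates tolerates a small stratum: the estimate is noisy but not systematically distorted. A logistic model fitted by maximum likelihood behaves differently. When deaths are few relative to parameters, a non-null odds ratio is pushed away from 1, and at the extreme the fit separates and gives no usable estimate. The push grows as the stratum shrinks.

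Research question 1 exists to compare strata. If telemedicine had the same mortality effect everywhere, a rare NYHA class could still show a stronger odds ratio than a common one simply because it is small. The sample size does not guard against this, because it was derived for a continuous outcome and not from deaths.

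**Working it through.** **1. The plan's own figure.** *Sample size calculation* uses 6.4 days, SD 21.1, type I error 5%, type II error 20% and 20% dropout. Per arm: 2 × (1.96 + 0.8416)² × 21.1² / 6.4² = 170.6, so 171, or 342 in total. Then 342 / 0.8 = 428. A t-based version gives 344 and 430. The stated 432 is reproduced closely. Then 432 × 12 = 5184 and 5184 / 0.8 = 6480, both exact. None of these figures concerns deaths.

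**2. Parameters (assumed coding).** Six continuous variables (age, BMI, LVEF, two blood pressures, heart rate) × 3 spline terms = 18. Sex plus 12 comorbidities = 13. SES 3, NYHA 3, aetiology 3, rhythm 2. Total 18 + 13 + 3 + 3 + 3 + 2 = 42. Within a stratum the stratifying variable drops out, for example 42 − 3 = 39 within an NYHA class. Hence about 40.

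**3. Deaths per stratum** = 6480 × share × mortality, with mortality assumed at 5% to 20%:

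| Stratum share | Deaths | Deaths per parameter (42) |
|---|---|---|
| 50% | 162–648 | 3.9–15.4 |
| 25% | 81–324 | 1.9–7.7 |
| 10% | 32–130 | 0.8–3.1 |
| 5% | 16–65 | 0.4–1.5 |
| 3% | 10–39 | 0.2–0.9 |

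The main cohort is restricted to newly diagnosed HF, which lowers these counts by an unstated amount.

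**4. Size of the distortion.** Simulation with 42 covariates, 40% on telemedicine, true odds ratio 0.70, and 200 to 600 replicates per cell. Entries are geometric mean odds ratios:

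| Stratum n | Deaths (8%) | Unpenalised | Firth | Deaths (15%) | Unpenalised | Firth |
|---|---|---|---|---|---|---|
| 1600 | 131 | 0.69 | 0.71 | 243 | 0.67 | 0.68 |
| 970 | 78 | 0.68 | 0.71 | 146 | 0.69 | 0.71 |
| 500 | 41 | 0.63 | 0.70 | 75 | 0.65 | 0.69 |
| 320 | 25 | 0.51 | 0.69 | 49 | 0.63 | 0.71 |
| 190 | 15 | 0.43 | 0.76 | 28 | 0.45 | 0.69 |

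In strata of 500 or fewer, some covariate coefficient diverged in 68% to 100% of unpenalised fits. Coverage of the 95% interval fell to 0.88–0.90 in the worst cells. Two further simulations, with about 9% and 10% deaths, gave unpenalised medians of 0.67 at n = 1000 and 0.60 and 0.52 at n = 300. In the 10% one, 61% of fits at n = 200 were at or near separation.

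**5. Null effect.** With a true odds ratio of 1.0 the geometric mean was 0.98–1.02 for n of 320 or more. At n = 190 it was 0.89 and 1.05, both within Monte Carlo error.

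**6. Bias against noise.** Where deaths were 50 or fewer, the log-scale bias ran from ln(0.63/0.70) = −0.11 to ln(0.43/0.70) = −0.49. The SD of the log odds ratio was 0.5 to 2.1.

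**7. Risk-difference scale.** In the simulation with about 9% deaths (true difference −0.026), standardised differences from the ordinary fit averaged −0.024 to −0.028. With 10% deaths (true −0.029), ordinary and Firth fits gave −0.029 and −0.030 at n = 500, and −0.037 and −0.036 at n = 300. Even that last case overstates by 0.037/0.029 − 1 = 28%. The log odds ratio at n = 300 overstates by ln 0.52 / ln 0.70 − 1 = 83%. Uncorrected Firth inflated mean predicted mortality: 0.130 against 0.090 at n = 300 in the former, and 0.140 against 0.10 in the latter.

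**8. Research question 2.** At an assumed uptake of 30% to 40%, recipients number 1944 to 2592. At 5% to 20% mortality that is 97 to 518 deaths against at least 42 + 6 = 48 parameters, or 2.0 to 10.8 per parameter. This is tighter than the overall analysis but milder than the smallest strata. It was not simulated.

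**The case against.** The strongest reply is that the defect is partly inferred. The splines, and the sentence adding the confounders to a model, belong to the primary linear model, as does stratified refitting. The wording about similar approaches covers functional status, health status and quality of life, and the mortality sentence follows without it. A condensed article may leave penalisation, spline terms and effect scale to an analysis plan that is not shown. This stands as a limit on certainty. It does not remove the point: the confounder list is introduced before any outcome model is named, mortality appears under the subgroup question, and an unadjusted mortality comparison in this observational cohort would be worse.

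Other limits also stand. In small strata, imprecision exceeds the bias, so wide intervals will often be the more visible result.

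Several stronger readings are tempting and are not supported:

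- *Every subgroup is affected.* Age is not stratified, and large strata such as sex should be little affected.
- *The smallest strata will show the largest effects.* They can, if a true effect exists. Mortality rate, uptake and stratum sizes are not given.
- *At most 6480 × 0.8 × 0.8 = 4147 patients are analysable.* The abstract plans to enrol 6480, and 20% dropout leaves 5184. Table 1 has mortality verified in the Personal Records Database, so dropout need not apply to it in full.
- *The plan commits to conditional odds ratios for mortality.* It names a model but no effect measure.

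**Conclusion.** The point holds in conditional form. If the 23 confounders, with splines, are refitted by unpenalised logistic regression within strata, those with roughly 50 deaths or fewer can have about as many parameters as deaths, or more. If a mortality effect exists, the odds ratio there is exaggerated (0.70 becoming 0.63 down to 0.43 in the cells simulated) or the fit fails, and unequal stratum sizes can then look like heterogeneity. Strata of about 1000 or more are little affected, and a null effect produces no systematic bias.

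Mortality, uptake, covariate coding, spline terms and stratum sizes are assumptions. The primary result is untouched: this is a secondary outcome in exploratory analyses, and the study objectives are framed on days alive without unplanned hospitalisation. It is a worthwhile, inexpensive improvement and not a threat to the study's main conclusions.

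**What to change.** For all-cause mortality in research questions 1 and 2:

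1. Report the standardised (marginal) 1-year risk difference for each subgroup or component contrast, as *Preparation of the statistical model* already does for functional status. This alone removes most of the distortion.
2. Where odds ratios are also reported, or deaths are few relative to parameters, use a Firth-type penalised fit. Before predicting absolute risks from it, correct the intercept (for example FLIC); otherwise predicted mortality is too high.

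The cost is a little more analysis code and slight shrinkage in the smallest strata (0.76 against a true 0.70 with 15 deaths). No data collection changes. Neither step makes a small stratum precise, so its interval should be read before its point estimate.

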##### Research question 2: effectiveness of different telemedicine components

Research question 2 investigates the effectiveness of the different forms of telemedicine intervention. We assess this question by performing three separate analyses in which intervention aspects are contrasted in the subset of participants that received telemedicine. The presence or absence of a telemedicine component is determined at a hospital level. The components of telemedicine that are contrasted are presence versus absence of a service centre, presence versus absence of an educational module, and high-intensity versus low-intensity protocol (table 2).

The population of interest is patients with newly diagnosed HF (maximum 3 months prior to baseline) who received telemedicine. Offering of telemedicine is measured at 6 months after baseline.

In addition to the set of confounding variables at the patient level used in the analysis above, confounding variables at the hospital level are considered because indication for telemedicine is expected to differ across hospitals. Confounding variables include academic or non-academic hospital, presence of a specialised heart centre, presence of an outpatient ward, size of outpatient ward (number of patients/year), staffing of the HF outpatient clinic and full-time equivalent of outpatient-ward staff.

For each of the three contrasts, the primary outcome model is fitted to estimate the average treatment effect of a component relative to the corresponding reference component on days of unplanned hospitalisation during 1 year in the population of patients with newly diagnosed HF that initiated telemedicine.

The secondary outcomes functional status, health status and hrQoL are assessed using similar approaches but using multinomial, probit and probit regression model, respectively. Healthcare utilisation and all-cause mortality will be assessed using Poisson regression model and binary logistic regression, respectively.

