### Progress and time plan

RELEASE-HF started in June 2021 and will last 4 years (figure 1). This study includes a collaboration with at least 29 hospitals that signed a letter of commitment. Additional hospitals may enter the study later if they can complete a 12-month follow-up per included patient through the HF registry.

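### Research question 2 tests three hospital-level components in separate models that do not adjust for each other, so components that occur together would share credit; its intervals should rest on the number of telemedicine hospitals

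*Protocol article*

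**What the plan says.** Under Research question 2, the article plans on "performing three separate analyses in which intervention aspects are contrasted in the subset of participants that received telemedicine". The contrasts are "presence versus absence of a service centre, presence versus absence of an educational module, and high-intensity versus low-intensity protocol". On the unit of exposure it says: "The presence or absence of a telemedicine component is determined at a hospital level". On the model: "For each of the three contrasts, the primary outcome model is fitted".

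That model comes from Preparation of the statistical model: "The primary outcome model is a linear mixed model with a random intercept for the participating centre", with continuous covariates as splines, and "Robust SEs are estimated to compute CIs". The type of robust estimator, the cluster level, the reference distribution and the degrees of freedom are not given.

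Research question 2 adds hospital-level confounders to the patient-level set: "Confounding variables include academic or non-academic hospital, presence of a specialised heart centre, presence of an outpatient ward, size of outpatient ward", followed by clinic staffing and full-time equivalents. That makes six. Neither this list nor the patient-level list names the other two components.

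On the number of hospitals, Progress and time plan says: "This study includes a collaboration with at least 29 hospitals that signed a letter of commitment". More may join. The number that offer telemedicine, which is the number that informs this question, is not stated.

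**The concern.** Objective 2 asks which components lead to more days alive without unplanned hospitalisation, and effective scenarios are to be proposed to hospitals nationally. That requires each component's effect to be separated from the others.

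A one-component model does not do this when hospitals with a service centre also tend to have an educational module or a high-intensity protocol. Co-occurrence is plausible from the article itself: Table 2 treats supplier, control centre, education and measurement protocol as features of one telemedicine package.

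Adjusting for patient characteristics cannot separate attributes that vary only between hospitals. The random intercept cannot either, because it treats the remaining centre effect as independent of the exposure. The planned multicollinearity check concerns confounders and telemedicine status, not the components against one another.

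A second issue follows from the same feature. The primary model was written for an exposure that differs between patients. Here the exposure differs only between telemedicine hospitals, so precision depends on how many there are, and six hospital covariates use up part of it. Some robust standard errors are too small in that setting.

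**Working it through.** **The plan's own figures.** No sample size or number of hospitals is given for research question 2. The stated chain serves the overall effect and patient-level interactions:

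- n per group = 2 × (1.96 + 0.8416)² × 21.1² / 6.4² = 170.6, so 171 and 342 in total (two-sided 5% assumed).
- Dropout: 342 / 0.8 = 427.5, so 428, against 432 stated. With 172 per group from the t distribution it is 344 / 0.8 = 430.
- 432 × 12 = 5184, and 5184 / 0.8 = 6480, both as stated.

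The chain reproduces closely but says nothing about hospital-level contrasts.

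**Bias from leaving out the other components.** With additive effects, the bias in one contrast is the sum, over the other two, of (effect of that component) × (its prevalence where the tested component is present minus its prevalence where it is absent).

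Assumptions, none given in the article: the tested component has no effect, the other two add 3 days each, each component is present in half of the hospitals, and latent correlation is r. The prevalence difference is then (2/π) × arcsin(r).

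- r = 0: difference 0, bias 0.
- r = 0.3: 0.6366 × 0.3047 = 0.194; bias 2 × 3 × 0.194 = 1.2 days.
- r = 0.6: 0.6366 × 0.6435 = 0.410; bias 2 × 3 × 0.410 = 2.5 days.

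Simulation agrees (2000 replicates, SD 21.1 from the article, intraclass correlation 0.02, no hospital covariates, about 1555 telemedicine patients, taken as 30% of 5184). SD here is the spread of the estimate. Coverage uses leverage-corrected standard errors and a t reference.

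| Hospitals | r | Estimate alone (truth 0) | Estimate adjusted | SD alone / adjusted | Coverage alone / adjusted |
|---|---|---|---|---|---|
| 20 | 0 | −0.03 | −0.05 | 2.20 / 2.00 | 94.0% / 94.9% |
| 20 | 0.3 | 1.14 | −0.05 | 2.15 / 2.08 | 91.5% / 93.6% |
| 20 | 0.6 | 2.52 | 0.09 | 2.13 / 2.39 | 78.8% / 92.0% |
| 29 | 0 | 0.00 | −0.02 | 1.89 / 1.78 | 94.0% / 93.9% |
| 29 | 0.3 | 1.21 | −0.07 | 1.93 / 1.77 | 89.2% / 94.8% |
| 29 | 0.6 | 2.42 | −0.04 | 1.91 / 2.08 | 75.0% / 93.5% |

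Correcting the standard error alone does not restore coverage when components are correlated. Adjustment largely does.

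**Interval coverage with few hospitals.** This is the same simulation approach with no effect of any component. The pair in each cell is for intraclass correlation 0.01 / 0.05. The uncorrected column is a cluster-robust standard error with 1.96. The corrected column is a leverage-corrected standard error with t on hospitals minus parameters.

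| Telemedicine hospitals | Uncorrected, no hospital covariates | Uncorrected, six covariates | Corrected, six covariates |
|---|---|---|---|
| 15 | 89.4 / 89.8% | 72.7 / 73.8% | 92.7 / 93.6% |
| 20 | 91.5 / 91.1% | 81.5 / 80.5% | 94.0 / 92.8% |
| 29 | 92.5 / 92.5% | 86.8 / 88.4% | 94.4 / 94.7% |
| 40 | 93.6 / 92.6% | 88.7 / 89.0% | 94.2 / 92.9% |

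Monte Carlo error is about √(0.87 × 0.13 / 2000) = 0.75 percentage points. A separate simulation (6000 replicates, 60 patients per hospital, intraclass correlation 0.02, six covariates) gave 81.8% at 20 hospitals and 87.8% at 29.

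**The case against.** **Co-occurrence is not documented.** The article reports no pattern of components across hospitals. If they are uncorrelated, the bias is zero. This stands, so the size is conditional. The planned analysis would not reveal which case applies, however, and the proposed cross-tabulation would.

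**The confounder list may not be closed, and components may be refined after the interviews.** That is possible. But the article fixes separate models and names its confounders, and the other components are not among them.

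**Intensity is partly a patient matter.** Table 2 lets the protocol depend on complaints or phase, and measurement frequency is also collected per patient. Even so, the article defines this contrast at hospital level for research question 2.

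**Joint fitting adds terms where hospitals are few.** Single-component contrasts can be a defensible trade of bias for precision. In the simulation at r = 0.6, the SD rises by 2.39 / 2.13 = 1.12 at 20 hospitals and 2.08 / 1.91 = 1.09 at 29. If components nearly coincide, a joint model cannot separate them. Both sets of results should therefore be shown.

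**The interval argument goes beyond the text.** A reader might infer that there are at most 29 hospitals, that large-sample standard errors are planned, and that the intervals are therefore too narrow. The documents do not support this. Twenty-nine is a minimum for all hospitals, the telemedicine subset is of unknown size, and the robust estimator is not named. An analysis plan that is not shown may specify a correction. The random intercept also accounts for clustering: model-based intervals covered about 93–96% in the simulation, though with variance components treated as known, which is optimistic. The low coverage figures need both an uncorrected estimator and all six hospital covariates.

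**Conclusion.** The mutual-adjustment point holds. As written, each contrast estimates a component together with whatever accompanies it, while the objective asks for component effects. The bias is 0 without correlation and about +1.2 to +2.4 days at latent correlations of 0.3 to 0.6, assuming 3 days for each of the other two. Those inputs are illustrative.

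A reader might instead put the 6.4 days from the sample size calculation on one omitted component. With a 50-point prevalence difference that gives 6.4 × 0.5 = 3.2 days. But 6.4 days is the assumed effect of telemedicine against none, so giving all of it to one component is an extreme case.

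The interval point holds only conditionally: uncorrected robust standard errors would undercover by an amount that depends on the unstated number of telemedicine hospitals. It is a detail to settle, not a demonstrated error. The coverage figures also do not carry over to research question 4, where intervals come from bootstrap percentiles. The mixing of components does carry over if the same one-at-a-time comparisons are used there.

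**What to change.** 1. Cross-tabulate the three components by hospital, and report the number of telemedicine hospitals at each level, before looking at outcomes.
2. Fit one model with all three components, or adjust each contrast for the other two, and report it beside the single-component results.
3. Where the table shows that components cannot be separated, report the effect as that of the bundle and do not attribute it to one component.
4. Name the inference for these contrasts: CR2 cluster-robust standard errors with a t reference, or Kenward-Roger or Satterthwaite with between-hospital degrees of freedom.
5. Keep hospital covariates few, chosen in advance, and enter continuous ones linearly.

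No new data are needed, because the interviews already cover all three components. The cost is analysis wording, two more hospital-level terms and wider intervals. With six hospital covariates, adding two terms takes the degrees of freedom from 21 to 19 at 29 hospitals, from 12 to 10 at 20, and from 7 to 5 at 15. The t multiplier relative to 1.96 then goes from 1.06 to 1.07, 1.11 to 1.14, and 1.21 to 1.31. The last pair shows why the other hospital covariates should be trimmed if few hospitals offer telemedicine.
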